#### Participant Recruitment

Patients are recruited during enrollment blocks, which correspond to the ED shifts of enrolled HCPs. After the patient was assessed by an HCP, a research team member approached eligible patients, introduced themselves, and presented the study without the HCP. Not all shifts will be covered, and providers were not informed of which shifts were sampled for enrollment. A research team member confirmed eligibility and obtained written informed consent from each adolescent and young adult and a waiver of parental consent for participants aged 18 years and younger, similar to other sexual health ED-based studies.

#### Randomization and Allocation

To avoid contamination, 50 HCPs were randomized 1:1 to the intervention (STIckER) or control arm. The allocation sequence was computer-generated by the study epidemiologist using a simple randomization method with stratification by location (adult vs pediatric ED). The randomization sequence was implemented by a study coordinator using a centralized allocation system. The assignment was not concealed from investigators. Randomization health care provider participant (HCP-P) in the intervention arm received 1:1 training with a research assistant on the STIckER app. If a participating provider left the ED before the end of the study period, a new provider randomized to the same study arm was invited to participate.

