### Intervention

Adolescents and young adults between the ages of 15 and 24 years attending the ED during the time that an HCP trained on STIckER was on service would scan the STIckER app before seeing the provider. patients as study participants (HCP-Ps and adolescent and young adult participants).

Adolescent and young adult participants are assigned to the arm of the provider to whom they are assigned. Adolescent and young adult participants with intervention-arm providers will scan a QR code with their personal mobile device, linking them to the web-based STIckER app. They will interact with the app, completing a sexual health assessment and indicating their personal values and preferences before being led to a final infographic to be shown to the HCP-P. This infographic will alert the provider to both the adolescent and young adult participants’ need for oral, rectal, or urinary STI testing and their preference for testing.

Adolescent and young adult participants with control-arm providers will also scan a QR code with their personal mobile device, but it will lead them to a landing page with a prompt informing them they can ask their provider about STI testing. They will not have access to the digital tools and shared decision-making modules within the STIckER app.

All adolescent and young adult participants are followed throughout the ED visit. Adolescent and young adult participants will complete questionnaires at enrollment and upon ED discharge. These questionnaires comprise a comprehensive set of predominantly validated instruments and will capture sociodemographic characteristics, sexual behavior, substance use, perceived HIV risk, patient satisfaction, and decision-making quality. HCP-P will also complete a questionnaire after each adolescent and young adult visit and an end-of-study questionnaire focused on STIckeR implementation.

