#### Adolescent and Young Adult Participants Study Assessments

#### Enrollment

At enrollment, enrolled adolescent and young adult participants will complete a basic questionnaire to collect data on age, race, ethnicity, sex at birth, gender identity, sexual preferences, the reason for the ED visit, if they had a primary care visit in the past year, and if they had a visit, did they receive an HIV or STI testing.

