### Statistical Analysis

We will summarize efficacy and implementation outcomes using standard descriptive statistics for continuous and categorical variables. We will conduct bivariate analyses to identify balance in the random allocation of the intervention across providers and patient characteristics.

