#### Preliminary Efficacy

An intent-to-treat analysis of all enrolled patients will be conducted according to random assignment of the intervention to estimate the effect of STIckER on STI testing. We will conduct a mixed-effects generalized linear model (GLM) with the logit link function to look at the effect of STIckER on STI testing, if there is a clustering effect by provider, or logistic regression if there is no provider effect. To determine whether there is a provider effect, we will assess the intraclass correlation coefficient (ICC) for the primary outcome using a null (empty) mixed-effects model with provider as a random effect. If the ICC is greater than 0.01, we will proceed with mixed-effects modeling; otherwise, we will use standard logistic regression. For other dichotomous outcomes, we will use the same analytic approach (GLM) with the logit link function if there is a provider effect or logistic regression if there is no provider effect.

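### Provider randomisation was stratified by ED and patients join after their provider's arm is fixed, but the stated primary model contains neither ED nor any baseline covariate

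*Protocol article*

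**What the plan says.** Under Randomization and Allocation, "50 HCPs were randomized 1:1 to the intervention (STIckER) or control arm", the sequence being generated "using a simple randomization method with stratification by location (adult vs pediatric ED". The same section states: "The assignment was not concealed from investigators".

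Patients are not randomised. Under Intervention, "Adolescent and young adult participants are assigned to the arm of the provider to whom they are assigned". Under Participant Recruitment, "After the patient was assessed by an HCP, a research team member approached eligible patients". The Intervention section places app use before the provider is seen. In either order, the provider's arm is already fixed when the patient is approached.

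Under Preliminary Efficacy, the primary analysis is a mixed-effects logit model if the provider ICC from a null model exceeds 0.01, and otherwise "logistic regression if there is no provider effect". No ED term and no baseline covariate is named. Patient and provider characteristics appear elsewhere in three places:

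- Statistical Analysis, as "bivariate analyses to identify balance in the random allocation of the intervention across providers and patient characteristics", with no stated consequence for the model.
- Exploratory and Subanalyses, as subgroup differences.
- Power Analysis, as variance assumed to be explained and covariates assumed to be balanced.

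The enrolment questionnaire records age, sex at birth and "the reason for the ED visit".

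**The concern.** A factor used to stratify randomisation normally belongs in the analysis model. If it predicts the outcome and is left out, the model-based standard error no longer matches the design. It is too large when ED mix is balanced between arms, and too small when whole providers fall to arms by unblocked chance, because ED is constant within provider.

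There is also a patient-level issue. Randomising providers protects the comparison of providers. It does not by itself balance the patients enrolled afterwards, whose approach and consent may depend on the arm. A prognostic patient factor that differs by arm biases an unadjusted comparison.

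ED differences also enter the null-model ICC, so a factor known in advance helps to decide which primary model is fitted.

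**Working it through.** **1. The plan's own figure.** Inputs from Power Analysis: J = 44 providers, N = 140 patients, ICC 0.01, R² = 0.5 at both levels, two-sided 5%, 80% power. With M = t(0.975, 42) + t(0.80, 42) ≈ 2.868:

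MDE = M × √[ICC(1−R²)/(0.25J) + (1−ICC)(1−R²)/(0.25N)]
= 2.868 × √[0.005/11 + 0.495/35] = 2.868 × 0.1208 ≈ 0.347, against 0.348 stated.

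With R² = 0: 2.868 × √[0.01/11 + 0.99/35] = 2.868 × 0.1709 ≈ 0.490, and power at 0.348 falls from 80.3% to 51.2%. The stated figure therefore counts on explanatory variables that the stated model does not contain.

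**2. Weight of ED (assumed rates, EDs of equal size).** At 50% and 20%, the overall rate is 35%. The ED share of outcome variance is (0.30/2)²/(0.35 × 0.65) = 0.0225/0.2275 = 0.099.

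**3. Type I error of plain logistic regression without ED, by formula.**
- *Unblocked providers:* 140/44 = 3.18 patients per provider, so the variance inflation is 1 + 2.18 × 0.099 = 1.216. Effective critical value 1.96/√1.216 = 1.777; two-sided error about 7.5%. Unequal patient numbers per provider raise it further.
- *ED mix balanced between arms:* 1.96/√(1−0.099) = 2.065; two-sided error about 3.9%.

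**4. By simulation (44 providers, 140 patients, 50%/20%, plain logistic regression).**

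| Allocation | Type I, without ED | Type I, with ED | Power at OR 2.7, without ED | Power, with ED |
|---|---|---|---|---|
| Unblocked | 8.8% | 5.3% | 69% | 76% |
| Balanced within ED | 3.9% | 4.9% | 77% | 80% |

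**5. Range over other assumed rates.** A separate simulation, unblocked, with a further prognostic patient factor in the data, gave type I error without and with ED of:
- 30%/30%: 5.0% and 5.1%
- 40%/20%: 5.8% and 4.7%
- 50%/15%: 10.3% and 5.4%

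Power at a conditional OR of 2.7 was 70% and 69%, 63% and 65%, and 57% and 62% respectively.

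**6. Chance imbalance of providers, if unblocked.** With 25 providers in a stratum, 2 × P(Bin(25, 0.5) ≥ 16) = 23% for a 16:9 split or worse. With 22, a 14:8 split or worse has probability 29%. If the patient ED mix were 60/40 in one arm and 40/60 in the other, the crude difference would move by 0.2 × 30 = 6 percentage points at 50%/20%, and by 0.2 × 20 = 4 points at 40%/20%.

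**7. The ICC rule.** In simulation without true within-ED clustering (50%/20%), the null ICC exceeded 0.01 in 84% of runs, against 43% when the EDs tested alike. Following the rule under unblocked allocation gave type I error between 4.1% and 5.5% across rates from 30%/30% to 50%/15% (800 runs each, Monte Carlo error about 1.5 points).

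**8. Recruitment.** If STI-related visits (assumed 70% tested, against 25% for others) differed by 5 to 10 points between arms, the bias would be 0.05 × 45 = 2.25 to 0.10 × 45 = 4.5 percentage points. With an assumed 0.3 SD arm difference in a prognostic factor and no true effect, type I error was 10–15% unadjusted, 9–11% with ED alone, and 5–7% with ED and that factor.

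**The case against.** **The section never says unadjusted, and a covariate list often sits in an analysis plan.** This is fair as far as it goes, and the 50% explained variance suggests that covariates may be intended. But the article specifies the primary model down to a numerical ICC switch and names randomisation by ED, so the missing stratum is a feature of the model as stated.

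**The plan's own rule already protects the type I error.** This largely stands. ED differences raise the provider ICC, the random intercept is then usually selected, and step 7 shows error close to 5%. The 9% figure belongs to the plain logistic branch only. The intercept treats the ED difference as unexplained provider noise and does nothing for patient case mix.

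**Adjustment does not narrow the interval of a log odds ratio.** Correct: the standard error rises from 0.36 to 0.39 when ED is added. A reader might infer from the 9.9% variance share that the unadjusted interval is 5% too wide (√0.901 = 0.949). That holds on the risk-difference scale, not for the planned logit model. The power gain comes from a larger conditional effect.

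**Simple randomisation with stratification is ambiguous.** It may or may not have been blocked, so both cases are shown. If allocation was balanced within ED, the probabilities in step 6 fall away.

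**Biased recruitment is not documented.** True. Non-concealment is stated for investigators. That recruiters knew the arm is a likely inference, since QR codes differ by arm and a research assistant trained intervention providers. Screening was open to any chief complaint, and providers were not told which shifts were sampled.

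**Conclusion.** The point holds as a worthwhile, low-cost improvement to the stated analysis. On the plain logistic branch, omitting ED moves type I error to about 9% (unblocked) or about 4% (balanced) at assumed rates of 50% and 20%, and costs about 7 or 3 points of power at an odds ratio of 2.7. With equal rates in the two EDs the effect is negligible. All testing rates here are assumptions.

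Three stronger readings are not supported:

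- That the primary analysis as a whole has an inflated error rate. The random intercept, when selected, absorbs most of it.
- That the estimate is confounded by ED. Under unblocked allocation, chance imbalance is random error, not systematic bias.
- That balance will be judged by significance tests that trigger adjustment. Statistical Analysis states neither a test nor a trigger.

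Recruitment after allocation is a real exposure of the design, but differential case mix is a possibility and not a documented fact.

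**What to change.** Fit the primary and secondary patient-level models with ED (adult/pediatric) as a fixed effect, plus a short covariate set fixed before the arm comparison is examined:

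- age and sex at birth, from the enrolment questionnaire;
- the recorded reason for visit, coded as STI-related yes or no by someone without knowledge of arm.

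Do not adjust for the 13-question sexual health assessment. Intervention patients complete it in the app, but controls only at exit, and it includes an item on gonorrhea or chlamydia testing in the previous 30 days. State whether provider allocation was blocked within ED, and label the resulting odds ratio as conditional on the covariates.

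The cost is a few degrees of freedom and a small coding task, since the yes/no variable is not described as already existing. Enrolment is complete and analyses were reported as underway, so the change should be dated and made before arms are compared. Adjustment reduces bias from recruitment after allocation; unmeasured selection would remain and should be acknowledged as a limitation.

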### Intervention

Adolescents and young adults between the ages of 15 and 24 years attending the ED during the time that an HCP trained on STIckER was on service would scan the STIckER app before seeing the provider. patients as study participants (HCP-Ps and adolescent and young adult participants).

Adolescent and young adult participants are assigned to the arm of the provider to whom they are assigned. Adolescent and young adult participants with intervention-arm providers will scan a QR code with their personal mobile device, linking them to the web-based STIckER app. They will interact with the app, completing a sexual health assessment and indicating their personal values and preferences before being led to a final infographic to be shown to the HCP-P. This infographic will alert the provider to both the adolescent and young adult participants’ need for oral, rectal, or urinary STI testing and their preference for testing.

Adolescent and young adult participants with control-arm providers will also scan a QR code with their personal mobile device, but it will lead them to a landing page with a prompt informing them they can ask their provider about STI testing. They will not have access to the digital tools and shared decision-making modules within the STIckER app.

All adolescent and young adult participants are followed throughout the ED visit. Adolescent and young adult participants will complete questionnaires at enrollment and upon ED discharge. These questionnaires comprise a comprehensive set of predominantly validated instruments and will capture sociodemographic characteristics, sexual behavior, substance use, perceived HIV risk, patient satisfaction, and decision-making quality. HCP-P will also complete a questionnaire after each adolescent and young adult visit and an end-of-study questionnaire focused on STIckeR implementation.

### STIckER Web-Based App

#### Control Participants

Participants in the control arm will scan a QR code and receive a statement reminding them they can always ask for STI testing.

#### Intervention Participants

Patient participants in the intervention arm will proceed through the following 5 modules (see Figure 1):

STI education**:** STIckER starts with a 1:06-minute video describing the importance of STI testing, followed by additional information about STIs and testing for STIs (see Figure 1).Sexual health assessment: Participants complete a 13-question assessment to assess their vulnerability to STIs. This assessment categorizes participants into high, medium, or low need for testing and generates recommendations for genitourinary, rectal, and oral gonorrhea and chlamydia testing at the time of ED visit (see Figure 1).Decision-making and shared-decision-making modules: Participants are taken through each recommendation with additional education and the option to opt in or opt out of testing (see Figure 1, panel C). Participants who are “intermediate need” for needing testing at that visit are taken to an additional shared decision-making module that accounts for individual values and preferences (see Figure 1).Provider display: STIckER ends with a hidden display uncovered when the provider places their finger over the STIckER logo to reveal it. This reveals testing recommendations and patient choices for oral, rectal, and urinary testing (see Figure 1).

**Figure 1. F1:**
[figure not shown]
Overview of the STIckER (STI Check in the Emergency Room) web-based application modules. STIckER is available online, and this version was frozen during the study [21]. Panel A: Educational module with introductory video and supplemental information about sexually transmitted infection (STI) testing. Panel B: Sexual health risk assessment stratifying participants by need for genitourinary, oral, and rectal testing. Panel C: Shared decision-making modules, including values clarification and opt-in/opt-out testing choices. Panel D: Provider-facing infographic summarizing participant testing needs and preferences, revealed by the provider via touch activation.

### Clinical Setting

This study was conducted in the adult and pediatric emergency departments of NewYork-Presbyterian/Columbia University Irving Medical Center, located in Northern Manhattan. These EDs collectively see more than 150,000 patient visits annually and serve a predominantly Hispanic patient population, with over 25% of patients living below the federal poverty line. The EDs provide safety-net care to many adolescents and young adults who lack consistent access to primary care. The high volume, demographic diversity, and prevalence of structural barriers to care in this setting make it particularly well-suited for piloting an intervention designed to support STI screening among underserved adolescent and young adult populations.

### Participants and Recruitment

The target enrollment for this study is 44 HCP-Ps and 140 adolescent and young adult participants.

For HCP-Ps, all ED attending physicians and physician assistants employed in the EDs, who work more than 5 shifts per month, are eligible. ED providers were recruited via a department-wide email request for participants. STIckER research coordinators will explain the study to interested HCPs and obtain written informed consent. HCP-Ps were selected to purposely sample half pediatric and adult ED providers with a range of professional experience.

For adolescents and young adult participants, all patients aged between 14 and 24 years, regardless of chief complaint, are eligible for screening. Adolescents and young adults aged between 14 and 24 years who self-reported sexual activity within the last 6 months and were able to speak English are eligible for enrollment. Participants who were in foster care, wards of the state, or in police custody, as well as those who were cognitively impaired, exhibited aggressive behavior, or were critically ill, as determined by their attending medical provider, were not eligible.

Research coordinators will screen ED patients during clinical hours by the enrolled HCP-Ps. Those times typically consisted of Monday-Friday, 8 AM-10 PM, with limited weekend enrollment. First, information to determine eligibility was gathered from the EMR (ie, age). Next, if a patient was deemed eligible to be assessed further, a research coordinator approached the patient to confirm criteria such as sexual activity and interest in the study. Eligible participants were enrolled with written informed consent. For participants aged between 14 and 17 years, we will obtain a waiver of parental consent and a 2-person verification of agreement to participate, such as the research coordinator and the physician attending the ED. Participants received a US $10 pay card at enrollment.

### Study Assessments

#### HCP-P Study Assessments

At enrollment, enrolled HCP-Ps will complete a basic demographic questionnaire. (age, race, ethnicity, sex at birth, gender identity, years since completing training, and type of clinical training completed).

The exit survey will be conducted immediately after a visit with an adolescent and young adult participant; the HCP-P will complete an exit survey.

HCP-Ps randomized to the control arm get questions on whether STI testing was discussed (“Did you and your patient discuss STI testing”), if the discussion was appropriate (Likert scale of 1‐5, from “completely appropriate” to “completely inappropriate”), if STI testing was ordered, and if STI testing was ordered what level of shared decision-making involvement occurred using the Control Preferences Scale (Likert scale of 1 to 5, from “I made the decision on my own” to “the patient made the decision on their own”) [22].

HCP-Ps randomized to the intervention will get the same questions on whether STI testing was discussed, if the discussion was appropriate, if STI testing was ordered, and if STI testing was ordered, what level of shared decision-making involvement occurred using the control preferences scale. They will also complete validated questions on implementation (acceptability of intervention measure [AIM], intervention appropriate measure [IAM], and feasibility of intervention measure [FIM]) [23].

The postsurvey will be conducted after completing their participation in the STIckER study (a maximum of 6 adolescent and young adult participants or the study completing overall enrollment), HCP-P will complete a postintervention questionnaire.

HCP-Ps, randomized to the control arm, will complete a self-efficacy questionnaire to measure their clinical communication skills [24].

HCP-Ps randomized to the intervention arm will complete the self-efficacy questionnaire measuring their clinical communication skills, a Perceived Characteristics of Intervention Scale (a 20-item assessment measure that covers 9 subconstructs: relative advantage, compatibility, complexity, trialability, observability, potential for reinvention, task issue, nature of knowledge, and technical support), a question on how easy it was To use the screen the participant showed them (Likert scale of 1 to 5, from “Complicated” to “Able to use the app immediately”), and open-ended questions about whether the STIckER app was acceptable and what changes they would like to see made [25].

#### Adolescent and Young Adult Participants Study Assessments

#### Enrollment

At enrollment, enrolled adolescent and young adult participants will complete a basic questionnaire to collect data on age, race, ethnicity, sex at birth, gender identity, sexual preferences, the reason for the ED visit, if they had a primary care visit in the past year, and if they had a visit, did they receive an HIV or STI testing.

